| Trial design                                              | 8  | 
The study will be a randomized controlled trial with parallel groups. Participants will be randomly assigned to one of three groups:
 
 
○ Control group: Participants who do not kiss after consuming an acidic beverage.
 
○ Experimental group 1: One member of the couple consumes an acidic beverage, and both partners kiss for 40 seconds.
 
○ Experimental group 2: Both members of the couple consume an acidic beverage and kiss for 40 seconds.
 
 
The results will be used to evaluate whether the act of kissing restores salivary pH more quickly than the time it takes for the body to do so physiologically. This design allows for clear comparisons of the effects of the different conditions, with an appropriate control group.
                                                                                                                                                                                                                                                                                                                                               |
| Methods: Participants, interventions, and outcomes |    |                                                                                                                                                                                                                                                                                                                                                                                                                                                                                                                                                                                                                                                                                                                                                                                                                                                                                                                                                                                                                                                                                                                                                                                                        |

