| Outcomes | 12  | 
Primary Outcome:
 
The primary outcome of this study is the time required for salivary pH to return to neutral levels (pH ~7) after the intervention (kissing). The objective is to demonstrate that the act of kissing facilitates a faster restoration of salivary pH compared to the physiological time required in the absence of a kiss.
 
Secondary Outcomes:
 
 
1. The salivary pH level measured at each time interval during the 40-minute observation period.
 
2. Comparison of salivary pH restoration rates between: 
 
o The control group and the two experimental groups.
 
o Experimental group 1 (only one partner consumes the acidic beverage) and experimental group 2 (both partners consume the acidic beverage).
 
 
 
 
Methods of Measurement:
 
A pH meter will be used to measure the hydrogen ion activity in the saliva, reflecting its acidity or basicity. The device employs a Toledo micro combined pH electrode with the following specifications:
 
 
o Measuring range: pH 0 - 14.
 
o Temperature range: 0°C - 80°C.
 
o Shaft dimensions: 60mm length and 3mm diameter.
 
o Glass membrane: U-type with resistance <600M at 25°C.
 
o Reference system: ARGENTHAL with Ag+ ion trap.
 
 
The saliva sample will be unstimulated to avoid pH alterations caused by increased salivary flow. A small sample volume is expected, and the thin electrode design ensures accurate measurement even in reduced quantities.
 
Measurement Timeline:
 
 
1. A baseline saliva sample will be collected before the participants consume the acidic beverage.
 
2. Immediately after ingesting the beverage, a second saliva sample will be collected.
 
3. Participants in the experimental groups will kiss for 40 seconds, while the control group will wait.
 
4. A saliva sample will be collected at 5-minute intervals for the next 40 minutes, resulting in a total of nine post-intervention samples per participant.
 
 
Justification:
 
Measuring salivary pH every 5 minutes is a standard approach in similar studies assessing the dynamics of salivary pH restoration. Additionally, measuring pH immediately after consuming acidic beverages is consistent with other research protocols. Using a pH meter ensures precise and objective measurements, while collecting unstimulated saliva minimizes alterations in pH caused by increased flow rate, enhancing the reliability of the data.
 |

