| Data collection methods                                   | 18a | 
The primary outcome of this study is the time required for salivary pH to return to neutral (pH 7.0) after the kissing intervention, compared to the control group. Baseline data, including the initial pH of unstimulated saliva before the intervention, will also be collected. Secondary outcomes include salivary pH measurements at defined time intervals (e.g., immediately after the intervention and every 5 minutes up to 40 minutes).
 
Data Collection Process:
 
 
○ Participants will expectorate saliva into sterile 3 mL conical Eppendorf tubes at each designated time point.
 
○ A calibrated pH meter will be used to measure the pH of the collected saliva. Calibration will be performed using standard buffer solutions at pH 4.01 and pH 7.01 before each data collection session, ensuring accuracy and reliability of the measurements.
 
○ All pH measurements will be conducted by trained members of the research team, who will follow a standardized protocol to minimize variability and ensure data quality. Duplicate measurements will be taken for 10% of the samples to verify consistency.
 
 
Data Recording:
 
 
○ Measured values will be entered directly into a secure, cloud-based Excel spreadsheet accessible only to authorized members of the research team. This ensures data integrity and confidentiality.
 
 |

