| Statistical methods | 20a | 
Analysis of Primary and Secondary Outcomes:
 
The primary outcome, the time required for salivary pH to return to neutral (pH 7.0), will be analyzed using appropriate statistical methods depending on the data distribution. First, tests of normality (e.g., Shapiro-Wilk test) will be conducted to determine if the data follows a normal distribution. If the data meets the assumptions for parametric tests, a one-way ANOVA will be used to compare the mean recovery times across the three groups: control, experimental group 1 (only one partner drinks the acidic beverage), and experimental group 2 (both partners drink the acidic beverage).
 
If the assumptions for ANOVA are not met, the non-parametric Kruskal-Wallis test will be applied to compare the groups. Post-hoc analyses (e.g., Tukey's HSD for ANOVA or pairwise comparisons with Bonferroni correction for Kruskal-Wallis) will be conducted to identify specific group differences.
 
For secondary outcomes, including salivary pH levels at specific time intervals, repeated-measures ANOVA will be used if the data meets parametric assumptions. Otherwise, the Friedman test will be employed to evaluate changes in pH over time within and between groups.
 
Additionally, pairwise comparisons will be performed to assess the differences in mean recovery times between the control group and each experimental group (control vs. experimental 1, and control vs.
                                                                                                                                                                                                                                                                                                                                                                                                                                                                                                                                                                                                                                                                  |

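### The Friedman fallback in item 20a cannot compare groups, so if parametric assumptions fail, pH levels over time have no valid between-group test

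*Protocol*

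**What the plan says.** The trial has three independent parallel arms (Protocol, item 8): "Participants will be randomly assigned to one of three groups". Saliva is sampled repeatedly, "resulting in a total of nine post-intervention samples per participant" (item 12).

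Item 12 names two secondary outcomes: the pH level at each interval, and restoration rates compared between groups. The first such comparison is between "The control group and the two experimental groups"; the second is between the two experimental groups. The term restoration rate is not defined.

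For these outcomes item 20a says that "repeated-measures ANOVA will be used if the data meets parametric assumptions", and that otherwise "the Friedman test will be employed to evaluate changes in pH over time within and between groups".

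The other non-parametric tests in item 20a belong to recovery time. For the primary outcome, "the non-parametric Kruskal-Wallis test will be applied to compare the groups", followed by Bonferroni-corrected pairwise tests. In addition, "pairwise comparisons will be performed to assess the differences in mean recovery times between the control group and each experimental group", by t-test or Mann-Whitney.

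**The concern.** The fallback gives the Friedman test two tasks, change over time and comparison between groups. It can do only the first. It is a one-factor test for related samples: each person is a block, the time points are ranked inside the block, and group membership does not enter the calculation.

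Two errors follow if the fallback is used as written. A real difference in pH level between kissing and control can go unseen. And the recovery expected in every arm after an acid challenge gives a very small p-value, which the protocol's wording allows to be read as a group result.

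**Working it through.** **The plan's own figure.** The protocol attaches no number to the Friedman test. Its one calculation, 30 participants for a one-way ANOVA (item 14), reproduces: at f = 0.76 and alpha 0.05, N = 30 gives power 0.9501 and N = 27 gives 0.9227. Nothing below rests on it.

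**Step 1: the statistic.** With n people, k time points and R_j the sum of within-person ranks at time j,

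χ² = [12 / (n·k·(k+1))] · Σ R_j² − 3n(k+1).

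Here k = 9 (item 12). Group appears nowhere. Adding a constant to all nine values of a person leaves that person's ranks unchanged, so every R_j and χ² are unchanged. This is algebra and needs no assumed figure.

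**Step 2: numerical check.** With 36 people and 9 time points, two of the three groups were shifted, one by 0.24 pH and one by 5 pH. The statistic was 2.7185 before and 2.7185 after.

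**Step 3: rising curves.** If every person's pH rises strictly through the nine samples, each person's ranks are 1 to 9, so R_j = n·j and Σ R_j² = n²·285. Then χ² = [12/(90n)]·285n² − 30n = 38n − 30n = 8n. For 36 people that is 288, on 8 degrees of freedom. Strictly rising curves give this value whether recovery is fast or slow, and whether or not the groups differ.

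**Step 4: rejection rates.** Inputs from the protocol: three groups, nine samples, 12 per group (item 14) or 15 per group (the couples target in item 10), and a shift of 7.10 − 6.86 = 0.24 pH with SD 0.18 (item 14). Assumptions: normal data, independent people, a linear rise over time, and an SD split of 0.13 between and 0.125 within person, so that √(0.13² + 0.125²) ≈ 0.18. The shift applies to both kissing groups. Each setting had 2,000 runs at the 5% level, with Friedman on the pooled data and Kruskal-Wallis on participant means.

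| Per group | Group shift (pH) | Rise over 40 min (pH) | Friedman | Kruskal-Wallis |
|---|---|---|---|---|
| 12 | 0 | 0 | 4.3% | 4.7% |
| 12 | 0.24 | 0 | 5.1% | 98.8% |
| 12 | 1.0 | 0 | 5.5% | 100% |
| 12 | 0 | 0.5 | 100% | 5.8% |
| 12 | 0.24 | 0.5 | 100% | 99.2% |
| 15 | 0.24 | 0 | 4.8% | 99.9% |
| 15 | 0 | 0.5 | 100% | 4.4% |

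Friedman stays near its nominal level whatever the group shift, and rejects always once pH changes over time.

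**Step 5: does another test in the plan fill the gap?** Kruskal-Wallis and Mann-Whitney are named for recovery time only. No other non-parametric test is given for pH over time. Running Friedman in each arm and setting the p-values side by side is not a between-group test.

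**The case against.** The strongest reply is that the fault is confined to one conditional branch for secondary outcomes. That is right. The primary outcome has a group comparison on both branches, and repeated-measures ANOVA can carry a group factor.

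A reader might also infer more than the protocol supports:

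- **That every between-group secondary comparison lacks a test.** If restoration rates mean recovery times, Kruskal-Wallis with Bonferroni covers all three pairs, and Mann-Whitney covers control against each experimental group. The gap is certain only for pH levels over time.
- **That non-normality alone triggers the fallback.** The trigger is failure of parametric assumptions; normality is only the check that is named.
- **That no group effect could move the statistic.** Exact invariance holds for a constant shift. The trial expects faster recovery, a difference in shape. With noise, or a plateau once pH is neutral, that can alter within-person ranks and move the pooled statistic. Friedman still could not attribute the movement to group.
- **That leaving out baseline pH as a covariate is part of the error.** Item 18a says "Baseline data, including the initial pH of unstimulated saliva before the intervention, will also be collected", and item 20a is silent on adjustment. Covariates are commonly settled in the statistical analysis plan, and an unadjusted randomised comparison is valid, if less precise.
- **That a time effect will be reported as a group effect.** The wording permits this; it does not make it certain.

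None of these removes the error in the sentence itself, which is a method stated wrongly and not a detail deferred to a later document.

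**Conclusion.** The point holds in limited form. As written, the non-parametric branch of item 20a gives no valid between-group test for pH levels over time, nor for restoration rates unless these are recovery times.

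The invariance to a constant group difference is exact and rests on no assumption. The rejection rates depend on the assumed SD split and the linear rise, but the contrast they show does not turn on those choices. The matter bears on secondary outcomes only, and only if the fallback is invoked. It should be corrected, but it does not threaten the primary analysis.

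**What to change.** In item 20a, restrict the Friedman test to change over time within a group. For the between-group comparison, name one of the following in advance:

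- **Kruskal-Wallis on one summary per participant.** Area under the pH curve addresses overall level; a recovery slope addresses rate. The test is already in the plan, so this is the smallest change.
- **Kruskal-Wallis at each time point with a multiplicity correction.** Bonferroni over nine samples would give 0.05/9 ≈ 0.0056 per test.
- **A rank-based longitudinal (ANOVA-type) analysis, or a permutation test,** with group and group-by-time effects. A permutation should reassign couples, since item 16c gives each pair one code for randomisation.

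State also whether restoration rate means recovery time or a slope, so that its test is unambiguous.

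The cost is a wording change and a little more analysis work. The samples needed are already planned, so no procedure or data item is added.

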| Sample size          | 14 | 
The sample size calculation was conducted using the G*Power statistical software (version 3.1.9.7, Fran Faul, Universität Kiel, Germany). The calculation was based on data obtained from the pilot study titled "Comparison of Salivary pH Changes after Consumption of Two Sweetened Malaysian Local Drinks among Individuals with Low Caries Experience: A Pilot Study". This study measured salivary pH changes after consuming acidic beverages and provided the necessary statistical parameters for sample size estimation.
 
Specifically, the following values from the pilot study were used:
 
 
Control group (mineral water): mean = 7.10, SD = 0.18.
 
Experimental group (local drink): mean = 6.86, SD = 0.18.
 
 
To calculate the effect size (<math>f</math>) for ANOVA, the means and standard deviations were combined using the formula:
 $n = \frac{(2 * (Z\beta + Z\alpha)^2 * \sigma^2)}{\Delta^2}$ 
Given the mean difference (7.10 - 6.86 = 0.24) and pooled SD of 0.18, <math>d=1.33d=1.33d=1.33</math>. Dividing by the square root of the number of groups (<math>k=3</math>), the resulting effect size was <math>f=0.76</math>, which is considered a large effect size.
 
The following input parameters were used in G*Power:
 
 
Effect size (<math>f</math>): 0.76 (large effect size based on observed data).
 
Alpha error probability (<math>\alpha</math>): 0.05.
 
Power (1-<math>\beta</math>): 0.95.
 
Number of groups: 3.
 
 
The output indicated that a total sample size of 30 participants is required to achieve a power of 95%, with 10 participants per group. To account for potential dropouts, an additional 20% will be recruited, resulting in a total of 36 participants (12 per group).
 
This effect size and resulting sample size are justified based on the observed differences in the pilot study, which measured salivary pH using similar methods (pH meter, unstimulated saliva samples in test tubes) and reported statistically significant differences between groups. Using this approach ensures that the sample size is both statistically adequate and logistically feasible for this study.
 |

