|                            |     | experimental 2). These comparisons will utilize independent t-tests if parametric assumptions are met or Mann-Whitney U tests if they are not.                                                                                                                                                                                                                                                                                                                                                                                                                                                                                                                                                                                                                                                                                                                                                                                                                                                                                                                                                                                                                                                                                                                                                                                                                                                                                                                                                                                                                                                                                                                                                                                                                                                                                                                                                                                                                                                                                             |

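### Item 20a tests the two kiss-versus-control contrasts twice, with a correction and then with none named, and does not say which set decides; as written this permits a family-wise error of about 9%

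*Protocol*

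**What the plan says.** Item 20a (Statistical methods) sets out three steps for recovery time.

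1. A one-way ANOVA across control, experimental 1 and experimental 2, or Kruskal-Wallis if the assumptions fail.
2. Post-hoc tests to locate the differences: Tukey's HSD after ANOVA, or "pairwise comparisons with Bonferroni correction for Kruskal-Wallis". Both cover all pairs, so they include each kissing group against control.
3. After the paragraph on secondary outcomes, a further step: "Additionally, pairwise comparisons will be performed to assess the differences in mean recovery times between the control group and each experimental group". The two contrasts are then listed by name, and the test is given: "These comparisons will utilize independent t-tests if parametric assumptions are met or Mann-Whitney U tests if they are not".

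Step 3 uses the same variable as steps 1 and 2. No adjustment, reduced alpha or dependence on the three-group result is named for it, and no sentence ranks step 2 against step 3. The only significance level in the protocol is in item 14 (Sample size): "Alpha error probability ( \alpha ): 0.05". Item 12 (Outcomes) makes recovery time the primary outcome and gives the aim as showing faster restoration with a kiss than without one.

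**The concern.** The trial's claim rests on these two contrasts. Step 2 protects them against multiplicity. Step 3 offers them again by tests that carry no protection unless some is added. Someone following the text could find a Tukey comparison non-significant and the t-test on the same contrast significant, and report the latter without departing from the protocol. The stake is the false-positive rate for the statement that kissing speeds recovery: with two separate 5% chances against a shared control, it is not 5%. With a real but moderate effect the two sets can also disagree, and the plan has no rule for that case.

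**Working it through.** **Inputs from the protocol.** Item 14 gives alpha 0.05, "Power (1- \beta ): 0.95", an effect size f of "0.76 (large effect size based on observed data", and "Number of groups: 3". Group size is 10 before and 12 after dropout in item 14, and 15 couples in items 2b and 10. Item 12 gives 5-minute sampling over 40 minutes.

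**Assumptions.** Two-sided tests (the sides are not stated), equal groups, one independent value per unit, and normal data for the t-tests.

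**The plan's own figure.** Noncentral F with k = 3 and lambda = f² × N = 0.76² × 30 = 17.3 gives power 0.9501 at N = 30, so the stated 30 reproduces. This confirms only that f = 0.76 leads to 30. How f was derived is a separate matter.

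**Family-wise error of step 3 as written** (both contrasts at 0.05, no gate, no true effect):
- Upper bound if the two tests were independent: 1 − 0.95² = 9.75%.
- Shared control and equal groups give the two statistics a correlation of 0.5. One minus the bivariate normal probability that both lie within ±1.96 is 9.07%.
- Simulated t-tests, 400,000 trials per group size: 9.08% (n = 10), 9.05% (n = 12), 9.10% (n = 15).
- Claiming an effect if either Tukey or the t-tests reject: the same 9.1%, because Tukey adds almost nothing beyond the t-tests.
- Mann-Whitney with times on a 5-minute grid, 10,000 trials, uniform distribution assumed: 8.2%, 8.7% and 8.4% at n = 10, 12 and 15. Lognormal times on the same grid gave 8.4% (n = 12) and 8.1% (n = 15).

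**The same two contrasts under other rules, no true effect:**

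| Rule | Family-wise error |
|---|---|
| Tukey only (step 2) | 3.6–3.7% |
| Holm | 4.6–4.7% |
| Dunnett (n = 12) | 5.1% (simulation error around a nominal 5%) |
| t-tests only after a significant ANOVA | 4.1–4.2% |
| Mann-Whitney only after a significant Kruskal-Wallis, 5-minute grid | 3.8–4.0% |

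The gate works because, with three groups, any two true pairwise nulls imply that all three groups are equal. The omnibus test then guards that case, and a single true null is tested at 5%.

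**Power per contrast at d = 1.33.** Item 14 supplies the d: "Given the mean difference (7.10 - 6.86 = 0.24) and pooled SD of 0.18", so 0.24 / 0.18 = 1.33. This is a pilot difference in pH between drinks, not an effect on recovery time, so the figures are illustrative.

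| Rule | 10 per group | 12 per group |
|---|---|---|
| Unadjusted t-test | 80% | 88% |
| Omnibus gate | 76% | 85% |
| Holm, both kissing groups have the effect | 76% | 85% |
| Holm, only one has it | 70% | 80% |
| Tukey | 69% | 79% |

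**The case against.** The protocol never says that the second set is unadjusted or tested at 0.05 each, nor that it runs whatever the omnibus result. A reader might infer a stated decision to test without correction; the text supports only silence. If the tests were meant to follow a significant three-group test, the error is about 4% and nothing is inflated. In the non-parametric branch there is a harmless reading: step 3 may simply name the test to which step 2's Bonferroni correction applies. Multiplicity detail is also often left to an SAP. Finally, item 14 sizes the trial for the three-group test, and item 12 lists control-versus-experimental comparisons of restoration rates as secondary, so step 3 could be called supportive.

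Part of this stands. The wording must be that the plan permits about 9%, not that it prescribes it. But the harmless reading fails in the parametric branch, where Tukey's HSD and independent t-tests are different procedures, and the linking word presents step 3 as an addition. Nothing labels step 3 supportive, and it is applied to mean recovery times, the primary variable. Nor is this detail left open for later: both procedures are already fixed here, and what is missing is the rule between them.

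A second tempting inference is that disagreement between the two sets under a real effect is itself evidence of inflated error. With both kissing groups shifted, the sets conflict on at least one contrast in 26% of simulated trials at d = 0.8 and 17% at d = 1.33 (12 per group). That reflects a difference in power. It shows why a deciding rule is needed, but it says nothing about Type I error, and d = 0.8 does not come from the protocol.

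**Conclusion.** The point holds as an ambiguity with a measurable consequence. Item 20a gives two procedures for the same two contrasts on the primary outcome and does not say which decides, or whether the second is corrected or gated. Taken literally, the second set allows a kissing effect to be declared with a family-wise error of about 9% by t-test and about 8 to 9% by Mann-Whitney. With an omnibus gate it would be about 4%. The figures assume two-sided 5% tests, equal independent groups and no true effect; they barely change across 10, 12 and 15 per group. The three-group test itself keeps its 5% level. The matter should be settled before data are seen, but it is not fatal, since a corrected analysis is already in the plan.

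**What to change.** Rewrite the pairwise part of item 20a so that control versus experimental 1 and control versus experimental 2 are tested once, under one named rule with a family-wise level of 5%. Any of these will do:
- Holm across the two contrasts;
- Dunnett within the ANOVA;
- t-tests or Mann-Whitney tests performed only after a significant three-group ANOVA or Kruskal-Wallis test.

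State that no claim will rest on any other unadjusted p-value.

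The change is one paragraph; sample size and procedures are untouched. Item 2b lists the trial as not yet recruiting, and item 25 provides the amendment route.

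The price is power per contrast. At the illustrative d = 1.33, the omnibus gate costs about 4 points at 10 per group (80% to 76%) and 3 at 12 (88% to 85%). Holm costs the same if both kissing groups benefit, but about 10 and 8 points if only one does (to 70% and 80%). Simply deleting the second set and letting Tukey decide also controls the error but costs most, about 11 and 9 points (to 69% and 79%). Dunnett lies between Tukey and the unadjusted test.
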